### Inclusion, exclusion, and diagnostic criteria

The inclusion criteria are shown in Table 1. The exclusion criteria are shown in Table 2. All recruited patients who meet the diagnostic criteria for LSS will be screened for eligibility in strict accordance with the inclusion and exclusion criteria.

**Table 1 Tab1:** Inclusion criteria

1) Lumbar MRI scan shows LSS at a single level (sagittal diameter of lumbar central canal < 13 mm; dural sac area < 100 mm^2^), with no prolapsed or sequestered discs.	
2) Recurrent intermittent claudication and unable to walk long distances.	
3) Aged 50–85 years and in need of pain relief.	
4) Inflammation-induced pain.	
5) Less than a 3-month history of radiating pain in the lower legs.	
6) LANSS score ≥ 12.	

*MRI*, magnetic resonance imaging; *LSS*, lumbar spinal stenosis; *LANSS*, Leeds Assessment of Neuropathic Symptoms and Signs

**Table 2 Tab2:** Exclusion criteria

1) Patients unable or unwilling to receive treatment	
2) Allergic to contrast medium or drugs planned to be injected	
3) Untreated local infection at the planned surgical site	
4) Patients who cannot cooperate during the procedure or have a history of mental disease	
5) Pregnancy	
6) Receiving anticoagulant therapy	
7) Congenital or surgical anatomical diseases which affect the safety and success of the procedure	
8) Systemic infection	
9) Severe respiratory or cardiovascular diseases	
10) Immunosuppression	

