**Fig. 1 Fig1:**
[figure not shown]
Schematic presentation of patient flow. LSS, lumbar spinal stenosis; CESI, caudal epidural steroid injection; SNRB, selective nerve root block; NRS, numeric rating scale; ODI, Oswestry Disability Index; LANSS, Leeds assessment of neuropathic symptoms and signs

The main outcome measures include the Leeds Assessment of Neuropathic Symptoms and Signs (LANSS) pain scale to determine whether the pain experienced is due to nerve damage, the Oswestry Disability Index (ODI) to assess functional status, and a numeric rating scale (NRS) for pain to evaluate pain intensity [20]. Two days before the procedure, we will assess the condition of patients using the LANSS pain scale, ODI, and NRS for pain. One day, 2 weeks, 3 months, 6 months, and 1 year after the procedure, we will evaluate these patients again using the NRS for pain and the ODI.

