### Interventions

Patients will be randomly divided into two groups: group A (patients will receive CESIs) and group B (patients will receive SNRBs). Two days before the procedure, we will assess the condition of patients using the LANSS pain scale, ODI, and NRS for pain.

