### Outcome measures

Multiple outcome measures were utilized which included the NRS (0–10 scale) pain scale and the ODI on a 0–50 scale, with assessment at 1 day, 2 weeks, 3 months, 6 months, and 1 year after the procedure. The Oswestry Disability Index (ODI): back pain-related dysfunction will be assessed using the ODI. The ODI contains 10 questions about daily activities, including inventories of pain intensity, personal care, lifting, walking, sitting, standing, sleeping, sexual life, social life, and traveling. Each question is rated on a scale from 0 to 5 points; the lower the score, the less disabled the person is by the pain. The NRS represented no pain with a 0 and the worst pain imaginable with a 10. NRS is an instrument for the self-assessment of pain and comprises a scale with 0 and 10 at either end of a straight line. The participants marked a point on the line to indicate their level of average pain. The value and validity of the NRS and ODI have been reported [28, 29]. The main outcome measures of the present study were ODI and NRS scores after follow-up and the final recurrence rate calculated according to the requirements. ODI and NRS scores were obtained by designated personnel after follow-up work. After obtaining the above two scoring data, the curative effect was evaluated according to the requirements of Table 4, and the recurrence rate was obtained. According to the ultimate purpose of this study, the recurrence rate plays a very important role in the outcome indicators. ODI and NRS also provide the basis for the final calculation of recurrence rate, which significantly affects the evaluation of the efficacy of each subject, and also plays a decisive role in the research results. Specific criteria for evaluating the efficacy are shown in Table 4.

**Table 4 Tab4:** Efficacy evaluation

Cured: neither CESI nor SNRB cured LSS	
Marked effect: NRS score < 2 points or ODI score < 50%	
Effective: NRS score 2–4 points or ODI score 50–70%	
Relapse: NRS score > 4 points or ODI score > 70% or the use of analgesics of the patient’s own choice	

*Note*: We will record the time a patient has recurrence and stop follow-up

*CESI*, caudal epidural steroid injection; *SNRB*, selective nerve root block; *LSS*, lumbar spinal stenosis; *NRS*, numeric rating scale; *ODI*, Oswestry Disability Index

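### Table 1 sets no minimum baseline NRS or ODI while Table 4 grades absolute follow-up levels, so a patient who enters below the relapse line and never changes counts as a non-recurrent success

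*Protocol article*

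**What the plan says.** **Entry.** Table 1 (Inclusion, exclusion, and diagnostic criteria) has six criteria. General pain need and function appear in words only: "Aged 50–85 years and in need of pain relief" and "Recurrent intermittent claudication and unable to walk long distances". The one scored symptom criterion is "LANSS score ≥ 12", and Methods/design gives that scale's purpose as "to determine whether the pain experienced is due to nerve damage". The same paragraph assigns pain intensity to the NRS and functional status to the ODI. Table 2 excludes nobody for a low NRS or ODI.

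**Baseline.** Both scores are nevertheless taken: "Two days before the procedure, we will assess the condition of patients using the LANSS pain scale, ODI, and NRS for pain" (Interventions; also Table 3).

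**Outcome.** Table 4 (Outcome measures) classifies follow-up scores as follows, with the ODI figures in per cent:
- The best class a patient can reach is given as "Marked effect: NRS score < 2 points or ODI score < 50".
- The class below it, still a success, is given as "Effective: NRS score 2–4 points or ODI score 50–70".
- Failure is given as "Relapse: NRS score > 4 points or ODI score > 70% or the use of analgesics". The analgesics meant here are those that patients take on their own initiative.

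The section says that the recurrence rate is obtained from this table. The Hypothesis section makes a lower recurrence rate with SNRB the trial's question.

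**The concern.** A recurrence is the return of something that went away. Table 4 requires neither a change from baseline nor an initial response, and Table 1 does not ensure that patients start above the line that later defines relapse. Some patients may therefore be classed as treated successfully although their condition is the same as on entry.

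Three things are at stake:
- The success proportion in each arm is overstated.
- The difference in recurrence between the arms is diluted, because patients below the line who stay there contribute no events in either arm.
- With about 38 patients per arm, a chance imbalance in such patients can move the comparison.

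**Working it through.** The plan has no figure of its own on this point, so the check has three parts: apply the rules as printed, bound the number of patients affected, and illustrate the dilution.

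**1. Table 4 applied to baseline scores that Table 1 allows** (ODI read as a percentage of the maximum score, no self-chosen analgesics)

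| Baseline NRS | Baseline ODI | Classes met before any injection |
|---|---|---|
| 1 | 30% | Marked effect |
| 3 | 40% | Marked effect (ODI) and Effective (NRS) |
| 4 | 60% | Effective |
| 4 | 70% | Effective |
| 5 | 40% | Marked effect (ODI) and Relapse (NRS) |
| 6 | 60% | Effective (ODI) and Relapse (NRS) |
| 7 | 75% | Relapse |

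The first four patients, if unchanged at every visit, are never a relapse. The fifth and sixth rows show that meeting a success class is not enough. Because the criteria are joined by *or*, a patient is clear of relapse only with NRS ≤ 4 **and** ODI ≤ 70% **and** no self-chosen analgesics.

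**2. How many might enter at NRS ≤ 4**

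The protocol gives no baseline mean or SD. Assumptions: NRS roughly normal, mean 5 to 8, SD 1.5 or 2.17. The value 2.17 is borrowed from the Sample size section, which does not present it as a baseline SD. NRS is treated as whole points, so the cut is at 4.5:

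share = Φ((4.5 − mean) / SD); count = share × 76

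| Mean | SD 1.5 | SD 2.17 |
|---|---|---|
| 5 | 0.369 (28.0 patients) | 0.409 (31.1) |
| 6 | 0.159 (12.1) | 0.245 (18.6) |
| 7 | 0.048 (3.6) | 0.125 (9.5) |
| 8 | 0.010 (0.8) | 0.053 (4.0) |

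Example: (4.5 − 6) / 2.17 = −0.691, and Φ(−0.691) = 0.245. The range is about 1% to 41%, or roughly 1 to 31 of 76. Each figure is an upper bound on the patients below every relapse line, since the ODI and analgesic conditions remove some.

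**3. What this does to the comparison**

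Assume that a share *f* in each arm enters below the line and stays there whichever injection is given. Assume also that true recurrence among the rest is 50% v 20%; the protocol states no expected rates. The observed rate is then p × (1 − f). For f = 0.10: 0.50 × 0.90 = 0.45 and 0.20 × 0.90 = 0.18. Power is for a two-sided 5% comparison of two proportions with 31 evaluable patients per group, the number the protocol states and which is taken here as given.

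| f | Observed recurrence | Difference | Power, 31 per group | n per group for 80% |
|---|---|---|---|---|
| 0 | 50% v 20% | 30 points | 71% | 39 |
| 0.10 | 45% v 18% | 27 points | 63% | 46 |
| 0.20 | 40% v 16% | 24 points | 56% | 54 |
| 0.30 | 35% v 14% | 21 points | 49% | 65 |

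The ratio of the two rates does not change; the difference and the power do.

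**The case against.** **The cause lies in Table 4, and entry severity is a design choice.** Largely true. If recurrence could follow only a documented response, an unchanged patient would not be a success even without an entry floor. The two tables have to be read together, and the fix therefore addresses both.

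**The population is symptomatic.** Participants are inpatients with claudication, limited walking, a need for pain relief and LANSS of at least 12. That makes the high end of the range less likely. It would also be wrong to infer that there is no minimum on any pain scale. But LANSS is used here to identify the type of pain, and none of these criteria bounds the two scores that decide relapse.

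**ODI percentages might be relative to baseline.** On that reading an unchanged patient sits at 100% and is a relapse. Table 4, however, refers to an ODI score and names no baseline, and the section describes the ODI as a 0–50 total. The NRS bands are in points on any reading.

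**Stronger readings that the documents do not support.** A reader might infer:
- That one arm is favoured. Randomization balances such patients in expectation, so what remains is dilution and chance imbalance.
- That these patients cannot show relief. NRS 4 can fall to 0, ODI can fall too, and both scores are main outcomes in their own right.
- That they would never relapse. A patient at NRS 4 is one point from the line, so constant *f* in the dilution table is a simplification.
- That the protocol yields an estimate of how many there are. It does not, because 2.17 is not given as a baseline SD and no baseline mean is stated.

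**It is late to change entry.** Recruitment began on 16 April 2020 and all work was due by the end of 2021. With 1-year follow-up, enrolment would have had to end around the end of 2020, before the article appeared in August 2021. This stands, and it makes the analysis part of the fix the practical one for this trial.

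**Conclusion.** The point holds. As printed, an eligible patient with, say, NRS 4, ODI 60% and no self-chosen analgesics who never changes is counted as effectively treated and free of recurrence on the endpoint that carries the hypothesis. The consequence is overstated success in both arms, a smaller recurrence difference with less power, and exposure to chance imbalance, without systematic bias towards either injection.

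The classification follows from the text alone. Its size does not: the 1% to 41% range rests on assumed means, SDs and normality, and the loss of power rests on assumed recurrence rates and on affected patients staying below the line. At a baseline mean near 8 the problem is a handful of patients at most; at a mean near 5 it would be substantial. It is a worthwhile, inexpensive correction rather than a flaw that invalidates the trial.

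**What to change.** 1. **Entry.** Add to Table 1 that, at the existing assessment 2 days before the procedure, the patient is above the trial's own relapse line: NRS > 4 or ODI > 70%. An NRS threshold alone would not mirror Table 4 and would turn away patients who are above the line only on ODI.
2. **Endpoint.** Count recurrence only after a documented post-injection fall below that line (NRS ≤ 4 and ODI ≤ 70%). This is also needed for patients such as NRS 6 with ODI 40%, who pass the entry line yet already meet *Marked effect* through ODI. Keep patients who never fall below the line in the denominator and report them as non-responders, so that lack of response is not read as lack of recurrence. State that the ODI percentages are of the maximum score, if that is what is meant.
3. **Patients already enrolled.** Report by arm how many were at or below the line at baseline, and repeat the recurrence comparison without them as a sensitivity analysis. The selection uses scores taken before the injection, so it does not depend on its effect.

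**Cost.** No new measurement is needed. Some mildly affected patients would not be enrolled, although the Sample size section calls the patient base large enough. The result would apply to more symptomatic patients. The sensitivity analysis has fewer patients in a trial of 76 and will be less precise, so it supports the main comparison and does not replace it.

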### Diagnostic criteria

According to the “Clinical Guideline for the Diagnosis and Treatment of Degenerative Lumbar Spinal Stenosis by the North American Spine Society (NASS)” in 2011: Degenerative lumbar spinal stenosis describes a condition in which there is diminished space available for the neural and vascular elements in the lumbar spine secondary to degenerative changes in the spinal canal.

The main clinical symptoms include sacroiliac joint pain and sharp radiating pain in the lateral thighs, lower legs, and feet, as well as lower extremity numbness and decreased muscle strength. Some patients also experience intermittent claudication. Leg pain and weakness are precipitated by walking or standing for a long time and relieved with forward flexion, sitting, and rest.

Magnetic resonance imaging (MRI) represents the gold standard for the assessment of LSS: sagittal diameter of the lumbar central canal, 13–15 mm (abnormal), 10–13 mm (narrow), and < 10 mm (absolute stenosis); dural sac area, < 100 mm^2^ (relative stenosis) and < 70 mm^2^ (absolute stenosis).

### Randomization and blinding

[name] and [name] from the Spine Department of the First Affiliated Hospital, School of Medicine, Shihezi University, will use computer software to generate random sequences, which will be sealed in envelopes and concealed from recruiters and subjects. [name] from the Second Spine Department and investigator [name] are responsible for recruiting eligible patients. [name] from the Second Spine Department will randomly assign recruited patients into two groups. In this study, we will use the single-blind approach in which the participant is unaware of which treatment he/she is receiving. The specific procedure performed will be kept hidden from all participants before unblinding.

We also plan to charge all subjects the same fee to ensure the nature of blinding. The specific fees charged are as follows: nerve blocks 86 yuan + 2 vials of triamcinolone acetonide injection (40 mg/ml, Kunming Jida Pharmaceutical Co., Ltd.), 18.98 yuan + 1 vial of lidocaine (20 mg/ml, Hebei Tiancheng Pharmaceutical Co., Ltd.), and 2.62 yuan + 1 vial of Omnipaque (300 mg I/ml, GE Healthcare, Shanghai, China) (83 yuan). The total cost is 190.6 yuan.

### Interventions

Patients will be randomly divided into two groups: group A (patients will receive CESIs) and group B (patients will receive SNRBs). Two days before the procedure, we will assess the condition of patients using the LANSS pain scale, ODI, and NRS for pain.

### Technique for caudal epidural injections

The patient will be asked to lie in the prone position. A soft pillow approximately 10 mm thick is placed under the stomach area so that the sacrum is slightly elevated. The sacral hiatus is identified and marked on the skin. Following correct skin sterilization and draping, a surgeon will first practice inserting a 7-gauge spinal needle. A subjective feeling of “give” and loss of resistance suggests piercing the sacrococcygeal ligament.

An 18-gauge spinal needle is then introduced into the anterior wall of the sacrum. Care is taken to ensure that the needle shaft is at an angle of 90° to the skin surface. Once the needle reaches the periosteum, it is tilted towards the caudal vertebra and advanced upward for up to 5 cm into the sacral canal with an angulation of 30° to the surface. The hub of the needle is then attached to the syringe. Loss of resistance when pushing air is characteristic of entering the sacral canal. After removal of the stylet and guidewire, and aspiration to check for blood or cerebrospinal fluid, 0.2–0.3 ml of Omnipaque is injected to confirm correct placement. If the contrast agent can be seen in the epidural space as confirmed by X-ray imaging, the needle is correctly placed. A mixture consisting of 80 mg of triamcinolone acetonide and 2 ml of 1% lidocaine is injected [22–24].

### Technique for nerve root blocks

The patient is placed in the prone position. The affected level is identified under C-arm guidance, and a horizontal line is marked at the level of the lower edge of the pedicle. After sterile preparation and draping, an 18-gauge spinal needle is inserted 0.5 cm below the marked line and 10 cm from the spinous process at an angle of 25–30° to the coronal plane and parallel to the intervertebral space on the axial plane. For local anesthesia, 1% lidocaine is injected when advancing the needle. Under C-arm guidance, the direction and depth of the needle are observed, and it is inserted where the nerve root exits. Anteroposterior and lateral X-ray imaging of the lumbar spine is performed again when inserting the needle through the intervertebral foramen. On the anterior-posterior view, the tip of the needle is placed approximately 0.5 cm beneath the corresponding pedicle. On the lateral view, the needle tip is positioned just below the pedicle and into 1/3 of the posterior aspect of the intervertebral foramen. Radiating pain along the nerve occurs if the nerve root is punctured. The patient is asked whether this is the site he/she experienced pain. Then, 0.2 to 0.3 ml of Omnipaque is injected into the nerve root sheath to clearly visualize the existing nerve root. When an adequate flow of contrast medium to the target area occurs, a solution consisting of 80 mg of triamcinolone acetonide and 2 ml of 1% lidocaine is injected [25–27].

### Data collection

We will evaluate the treatment outcomes using the NRS and ODI 1 day, 2 weeks, 3 months, 6 months, and 1 year after the procedure. The treatment plan and evaluation of results are shown in Table 3.

**Table 3 Tab3:** Treatment plan and evaluation of results

Data collection/recording	Person in charge	Observational phase		Follow-up phase			
		2 days before intervention	1 day after intervention	2 weeks after intervention	3 months after intervention	6 months after intervention	1 year after intervention
Obtaining informed consent	[name]	×					
Collecting patients’ basic information and medical history	[name]	×					
Screen patients for eligibility	[name]	×					
LANSS pain scale	[name]	×					
ODI	[name] [name]	×	×	×	×	×	×
NRS for pain	[name] [name]	×	×	×	×	×	×

*LANSS*, Leeds Assessment of Neuropathic Symptoms and Signs Pain Scale; *ODI*, Oswestry Disability Index; *NRS*, numeric rating scale

### Outcome measures

Multiple outcome measures were utilized which included the NRS (0–10 scale) pain scale and the ODI on a 0–50 scale, with assessment at 1 day, 2 weeks, 3 months, 6 months, and 1 year after the procedure. The Oswestry Disability Index (ODI): back pain-related dysfunction will be assessed using the ODI. The ODI contains 10 questions about daily activities, including inventories of pain intensity, personal care, lifting, walking, sitting, standing, sleeping, sexual life, social life, and traveling. Each question is rated on a scale from 0 to 5 points; the lower the score, the less disabled the person is by the pain. The NRS represented no pain with a 0 and the worst pain imaginable with a 10. NRS is an instrument for the self-assessment of pain and comprises a scale with 0 and 10 at either end of a straight line. The participants marked a point on the line to indicate their level of average pain. The value and validity of the NRS and ODI have been reported [28, 29]. The main outcome measures of the present study were ODI and NRS scores after follow-up and the final recurrence rate calculated according to the requirements. ODI and NRS scores were obtained by designated personnel after follow-up work. After obtaining the above two scoring data, the curative effect was evaluated according to the requirements of Table 4, and the recurrence rate was obtained. According to the ultimate purpose of this study, the recurrence rate plays a very important role in the outcome indicators. ODI and NRS also provide the basis for the final calculation of recurrence rate, which significantly affects the evaluation of the efficacy of each subject, and also plays a decisive role in the research results. Specific criteria for evaluating the efficacy are shown in Table 4.

**Table 4 Tab4:** Efficacy evaluation

Cured: neither CESI nor SNRB cured LSS	
Marked effect: NRS score < 2 points or ODI score < 50%	
Effective: NRS score 2–4 points or ODI score 50–70%	
Relapse: NRS score > 4 points or ODI score > 70% or the use of analgesics of the patient’s own choice	

*Note*: We will record the time a patient has recurrence and stop follow-up

*CESI*, caudal epidural steroid injection; *SNRB*, selective nerve root block; *LSS*, lumbar spinal stenosis; *NRS*, numeric rating scale; *ODI*, Oswestry Disability Index

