Most patients seeking treatment for lower back pain have LSS. Treatments for LSS can be conservative and surgical. Conservative management is successful in most patients and is recommended as first-line treatment. Common conservative treatments for LSS include caudal epidural steroid injections (CESIs) and selective nerve root blocks (SNRBs). The reasons for their popularity among primary care physicians are as follows: First, compared with conventional surgical interventions, SNRBs and CESIs greatly reduce the time that physicians are exposed to X-rays, thus protecting their health. Second, SNRBs and CESIs are easy to perform and have a short learning curve.

The efficacy of CESIs has been demonstrated in many studies. Delport et al. analyzed 140 patients treated with epidural steroid injection (ESI) [11]. Fifty-three percent reported improvement in their functional abilities and 74% were at least somewhat satisfied with ESI as a form of treatment. Fukusaki et al. conducted a prospective, randomized, double-masked trial evaluating the efficacy of ESI in 53 patients with LSS [12]. The patients were randomized into three groups: epidural saline injection, epidural local anesthetic, and epidural anesthetic plus steroid. They found that there was a significant difference in the efficacy of the different treatments at 1 month. However, after 3 months, there was no significant difference between the three groups, proving the short-term effect of ESI. Koc et al. reported findings from a prospective, randomized controlled trial of 33 patients comparing the effects of ESI and a conservative inpatient physical therapy program on pain and function for patients with LSS [13]. They found that the ESI group had significant improvement in visual analog scale (VAS) scores at the 2-week follow-up. They concluded that ESI and physical therapy are equally effective in treating LSS up to 6 months of follow-up, while ESI has better short-term efficacy.

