A selective nerve root block (SNRB) is a minimally invasive procedure; a needle is inserted into the epidural space in the foramen at the suspected spinal level, and medications such as steroids and local anesthetics are then injected into the area of a specific nerve root [14]. This procedure is considered a very safe and effective treatment option for spinal neuropathy and chronic back pain [15, 16]. Zhang et al. performed SNRBs in 56 LSS patients and found that 80% of them achieved excellent short-term surgery outcomes [17]. Weiner et al. analyzed 30 patients with herniated discs who underwent nerve root blocks and noted immediate relief in 27 patients. During 1–10 years of follow-up, 22 patients (79%) experienced substantial and permanent pain relief [18]. Martin et al. retrospectively analyzed 30 (20 disc herniations, 10 foraminal stenoses) patients with minor sensory/motor deficits who were treated with a SNRB [19]. They found that 87% of patients had rapid and significant regression of pain in 1–4 days, and 60% had permanent resolution of pain. Therefore, they believe that SNRBs are very effective in treating lumbar neuropathy and recommend them as the treatment of choice for this condition.

Narrowing of the spinal canal caused by lumbar spine degeneration usually occurs slowly, over many years or decades. Substantial narrowing compresses the spinal nerves, which causes symptoms including pain at the early stage, and numbness and weakness of the extremities at the middle and late stages, severely affecting patients’ quality of life. Therefore, doctors should aim for early-stage interventions, offer effective treatments in the middle stage, and absolutely avoid late-stage surgery. In addition, it is recommended that patients in need of conservative treatments receive interventions as early as possible to prevent exacerbation of lumbar neuropathy.

It follows from the above that both CESIs and SNRBs can effectively relieve clinical symptoms and improve neurologic function in patients with LSS. SNRBs are different from epidurals. Instead of administering medication to cover all the nerve roots, selective blocks are performed to target a particular pinched nerve root. SNRB injections can therefore be performed to manage a specific area of pathology without causing damage to nearby normal nerve tissues.

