## Discussion

Both SNRBs and CESIs have proven efficacy against LSS. However, there are no studies comparing the effectiveness of these two treatments in LSS. In clinical practice, primary care physicians often have to choose between these two procedures based on their own experience as there is no guideline for them to refer to. Such subjectivity raises the risk of adopting a suboptimal treatment plan for a patient, which can result in less than desirable outcomes and increase the uncertainty surrounding the prognosis of patients. In severe cases, treatment can fail, increasing patients’ pain and economic burden. To avoid patients receiving inappropriate treatment, we evaluated the effects of SNRB and CESI treatment for LSS. We will divide recruited LSS patients into two groups and offer them either SNRBs or CESIs. Data including duration of symptom relief and time to relapse in patients in the two groups will be recorded, and the recurrence rate will be calculated to determine whether SNRBs or CESIs are more effective in relieving patients’ symptoms long term. We hope our findings will provide a reference for physicians and help them make a choice between SNRBs and CESIs for LSS patients based on scientific and clinical evidence so that these patients can receive optimal treatment with maximal efficacy.

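### Table 4 scores Relapse on current status alone, so the recurrence rate mixes patients who never responded with patients who recurred after relief

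*Protocol article*

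**What the plan says.** The Hypothesis section and the opening of Methods/design make recurrence the quantity of interest. Background and Discussion add how long relief lasts; the Discussion states: "Data including duration of symptom relief and time to relapse in patients in the two groups will be recorded".

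Outcome measures then fixes how recurrence is obtained. NRS and ODI are collected and "the curative effect was evaluated according to the requirements of Table 4, and the recurrence rate was obtained". The Table 4 categories are:

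- "Relapse: NRS score > 4 points or ODI score > 70% or the use of analgesics" (analgesics chosen by the patient);
- "Effective: NRS score 2–4 points or ODI score 50–70" per cent;
- "Marked effect: NRS score < 2 points or ODI score < 50" per cent;
- a cured row, which states only that neither procedure cures the condition.

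The note to the table adds: "We will record the time a patient has recurrence and stop follow-up".

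Data collection and Outcome measures list assessments at 1 day, 2 weeks, 3 months, 6 months and 1 year. Table 3 places the 1-day assessment under the observational phase and starts the follow-up phase at 2 weeks. Table 1 sets no minimum NRS or ODI for entry, although it requires a LANSS score of at least 12, claudication and a need for pain relief.

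**The concern.** Recurrence means that a symptom went away and came back. The Table 4 rule looks only at where the patient stands at a visit. It does not ask whether the patient was ever better, and it does not use the scores taken 2 days before the procedure. With no category for non-response, persistent failure has nowhere to go except Relapse.

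The outcome that carries the hypothesis therefore answers a different question from the one asked. A lower rate with SNRB could reflect more patients responding at the start, more durable relief in those who respond, or both, and the single rate cannot say which. Time to relapse has the same fault: for a patient who never improved it is simply the date of the first scored visit, not a duration of relief. Because follow-up stops at the event, a patient who responds late is lost and cannot be reclassified from the data.

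**Working it through.** **1. Does the rule separate the two kinds of event?** Apply Table 4 to patients whose scores never change.

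| Scores before and at every visit | Table 4 category | Actual course |
|---|---|---|
| NRS 7, ODI 80% | Relapse only | never relieved |
| NRS 3, ODI 60% | Effective only | no change |
| NRS 7, ODI 40% | Relapse and Marked effect | never relieved |

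The first patient is a recurrence without any relief to recur from. The second is a treatment success without any improvement. The third shows that the criteria overlap, because they are joined by *or* and no order of precedence is given.

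**2. How does mixing affect the rate?** Let f be the share of an arm that is never relieved and r the recurrence among those who are. The scored rate is

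scored = f + (1 − f) × r.

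With the same r in group A (CESI) and group B (SNRB), the difference is

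(fA − fB) × (1 − r),

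which is not zero unless fA = fB or r = 1.

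**3. Inputs.** The plan states no expected recurrence rate, so there is no figure to reproduce. The sample size rests on a continuous score and is not affected. All values of f and r below are assumptions.

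**4. Assumed values.**

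- fA = fB, same r: spurious difference 0.
- fA = 0.30, fB = 0.10, r = 0.40 in both: A = 0.30 + 0.70 × 0.40 = 0.58; B = 0.10 + 0.90 × 0.40 = 0.46. Difference 12 points, with equal true recurrence.
- Masking: fA = 0.10, rA = 0.50; fB = 0.30, rB = 0.30. A = 0.10 + 0.90 × 0.50 = 0.55; B = 0.30 + 0.70 × 0.30 = 0.51. A true 20-point difference in recurrence appears as 4 points.

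**5. Range from the Background series, r = 0.30 assumed in both arms.** For epidural injection: "Fifty-three percent reported improvement in their functional abilities and 74% were at least somewhat satisfied with ESI as a form of treatment". Taking complements, fA is 0.47 or 0.26. For SNRB, one series reports 80% with excellent short-term outcomes, and of another the protocol says: "They found that 87% of patients had rapid and significant regression of pain". Complements give fB of 0.20 or 0.13.

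| fA | fB | Scored A | Scored B | Difference |
|---|---|---|---|---|
| 0.47 | 0.13 | 0.629 | 0.391 | 23.8 points |
| 0.47 | 0.20 | 0.629 | 0.440 | 18.9 points |
| 0.26 | 0.13 | 0.482 | 0.391 | 9.1 points |
| 0.26 | 0.20 | 0.482 | 0.440 | 4.2 points |

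The answer runs from about 4 to 24 points depending on which proxy is chosen. These series measured function, satisfaction, overall outcome and pain regression in different populations (the 87% series was 20 disc herniations and 10 foraminal stenoses). None measured non-response as Table 4 would define it.

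**The case against.** **Relapse already implies earlier relief.** In ordinary language it does. But then a patient with persistently high NRS and ODI has no category at all, so the table fails on that reading too. Reading the ODI percentage as a percentage of baseline does not help: the NRS and analgesic criteria remain absolute, and any one of them is enough.

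**Scores above threshold at any time, counted in all randomised patients, make a legitimate comparison.** This stands. The Discussion also asks which procedure relieves symptoms better in the long term, and an all-randomised failure endpoint serves that aim. A reader might infer that the randomised comparison is invalid or the trial's conclusion necessarily wrong. The protocol does not support that. The defect lies in calling the composite recurrence and drawing a conclusion about recurrence from it. NRS and ODI are also main outcomes, and relapse times are recorded, so part of the distinction could be recovered, though not for patients whose follow-up ended early.

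**Day 1 may not count.** This also stands. A reader might infer that every non-responder is certainly scored as a recurrence on day 1. Two sections list day 1 among the outcome assessments, but Table 3 puts it in the observational phase and no sentence says that a day 1 score triggers relapse. It is possible, not established. It matters if it applies, because the 87% series saw pain regress over 1 to 4 days, so someone about to respond could be removed from follow-up.

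**Conclusion.** The point holds as a fault in a stated rule, not as missing detail. Table 4 as written counts patients with persistently high scores as recurrences, can count unchanged patients as successes, and stops observation at the event. The recurrence rate and time to relapse therefore do not isolate what the hypothesis and the stated interest in duration of relief refer to.

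The size cannot be estimated from the protocol. With equal true recurrence the spurious difference is (fA − fB)(1 − r): nil if initial non-response is balanced, and 12 points under one plausible set of assumed values. A reader might take the upper end of the Background-based range, 19 to 24 points, as the expected bias. That is not supported: it pairs non-comparable series and one assumed r, and another figure in the same Background sentence brings it down to 4 to 9 points. The conclusion about the definition depends on none of these numbers.

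**What to change.** 1. Name the main event treatment failure by 1 year, and keep every randomised patient in the denominator.
2. Report its two parts separately. Initial non-response: define response at 2 weeks relative to the pre-procedure NRS and ODI, with a rule for cases where the two scales point to different categories. Recurrence: first meeting Relapse at a later visit after a response. Using the present Table 4 categories at 2 weeks without baseline would repeat the defect.
3. Reserve the words recurrence and duration of relief for the second part, and treat it as descriptive, because restricting to responders breaks the randomised comparison.
4. Do not let a day 1 score alone set the event, and continue the scheduled NRS and ODI assessments after the event.

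Cost: a documented endpoint amendment, which should be settled without sight of results by arm, since recruitment began in April 2020; continued collection of visits that are already scheduled; and fewer events for the recurrence part. For any patient whose follow-up was already stopped before 2 weeks, the split cannot be made from existing data, and the number of such patients in each arm should be reported.
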